#### Strategies to improve adherence to the intervention {11c}

Treatment compliance is monitored through pill counts and regular contact with participants, with instructions to adjust medication dosage at weekly outpatient clinic visits. All the patients were treated in an outpatient setting and received 7-day supplies of the medication in seven individual packages. They returned the empty packages at the end of each week to exchange them for the next week’s supply, until the treatment ended.

#### Relevant concomitant care permitted or prohibited during the trial {11d}

Most participants are treated as outpatients receiving conventional and standard cares such as rest and pain relief. Family members are responsible for monitoring the patients for progress in neurological symptoms such as worsening headaches. If a patient is reported to have worsening symptoms, he or she will be further evaluated by two attending physicians for neurological deficits. These patients may be admitted during the trial for the treatment of progressing neurological deficits and discharged when their symptoms are relieved significantly.

Within 72 h prior to treatment, CT, routine blood test, coagulation, blood glucose and biochemical analysis were rechecked before enrolling into the group, as well as neurological assessment. At the end of 2 weeks and 4 weeks, routinely check blood test, coagulation, blood glucose and biochemical analysis and re-evaluate neurological function. CT scans are performed at end of 2 weeks, 4 weeks and 3 months. mRS and ADL-BI were scored before treatment and at the end of 4 weeks, 3 months and 6 months.

Each patient receives an in-person clinical assessment at an outpatient clinic by two attending neurosurgeons who are kept blind to the treatment allocation, every 2 weeks during the 28-day treatment duration, and then each month thereafter until 180 days post-randomization.

Anticoagulants (warfarin or new oral anticoagulants) are prohibited. Antiplatelet drugs (aspirin, clopidogrel) or Xuesaitong (traditional Chinese medicine for activating blood circulation) can potentially interfere with haematoma absorption and are not recommended during the treatment. However, these patients will not be exclusively excluded from the trial participation. The following drugs may potentially interact with statins and/or cause adverse events and will not be recommended during the treatment: red yeast rice, erythromycin, fibrates, cyclosporin, macrolide antibacterials, azole anti-fungals, tacrolimus, gemfibrozil, troglitazone and itraconazole.

The use of other medications is recorded in the case report form (CRF), including their name, dose and duration of treatment. Any change in haematological and biochemical markers, such as liver function tests, and side effects, such as myalgia, constipation and other possible drug-related symptoms, will be recorded. All details of any treatment during the 180-day study period are recorded.

#### Provisions for post-trial care {30}

If a patient develops serious complications related to the experimental drugs, we will arrange for the patient to be hospitalized until the related symptoms are fully resolved.

### Outcomes {12}

The primary outcome is a composite of ‘good outcome’, including any reduction in subdural haematoma volume from baseline and free of surgery and death within 28 days of the treatment. The haematoma volume is measured centrally using the Tada formula of maximal length (L) × maximal width (W) × maximal thickness (H), divided by 2 [23], on the acquired CT images by 3 independent neuroradiologists blind to the treatment location. Details of the location, density and compartment of the haematoma are also recorded.

Secondary outcomes include functional outcome according to a ‘shift’ in the distribution of the full range of scores on mRS at 28 days; function on the modified Barthel Index measure of actives of daily living (ADL-BI) at 28 days; surgical intervention at 28, 90 and 180 days; and reduction in haematoma volume at 14, 28 and 90 days.

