#### Criteria for discontinuing or modifying allocated interventions {11b}

Eligible patients are centrally randomized in a 1:1 allocation ratio to intervention (atorvastatin combined with low-dose dexamethasone) and control (atorvastatin combined with matching placebo) groups using a blocked randomization method via a data acquisition system for electronic data capture (DAS for EDC, version 5.0) developed by Stemexcel Technology Co. Ltd., Beijing.

If a participant develops any form of neurological deterioration (e.g. altered level of consciousness) that is suggestive of expansion of the haematoma, they may be admitted to the hospital for assessment and treatment until their symptoms are relieved or resolve. If surgery is undertaken for a deteriorating patient, the randomized oral study medication is to be resumed as soon as possible after the operation until the end of the planned 28-day treatment period.

The patient has the right to refuse treatment at any time or to withdraw completely from the trial. The investigator can also ask the patient to withdraw from the trial, including (1) the compliance of the subjects was poor and the scheme was violated, (2) unacceptable adverse reactions/serious adverse events occur, (3) subjects experienced serious complications during the trial and urgent measures were required, (4) the subject withdraws from the clinical trial or withdraws the informed consent form and (5) other special circumstances.

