### Participant timeline {13}

Baseline demographic and clinical features, including medical history, severity and type of neurological deficit and physical and biochemical results, are collected at the time of enrolment in the study. Treatment should be initiated immediately after randomization (Table 1). All background care should follow standard guideline recommendations for the management of CSDH in China which includes the withholding of anticoagulation and use of antiplatelet agents and prescribing prophylactic antiepileptic drugs and regular use analgesics. Protocol-mandated assessments will be performed according to the schedule (Table 1), and the study flow chart illustrates key steps in the trial (Fig. 1).

**Table 1 Tab1:** Visit and assessment schedule

Items	Screen	Day 1	Day 7 ± 1	Day 14 ± 1	Day 28 ± 3	Day 90 ± 7	Day 180 ± 7
Informed consent	×						
Inclusion/exclusion^a^	×						
Filling general information	×						
Collect medical history	×						
Concomitant medications^b^	×	×	×	×	×		
Physical examination	×						
Surgery		×	×	×	×	×	×
Neurological symptoms^c^	×	×	×	×	×	×	×
Haematoma volume^c^	×			×	×	×	
mRS^c^	×				×	×	×
ADL-BI					×	×	×
Blood routine	×	×		×	×		
Biochemistry	×	×		×	×		
Coagulation	×	×		×	×		
Vital signs^c^	×	×	×	×	×		
Electrocardiography	×			×	×		
Adverse events		×	×	×	×	×	×
Allocate random number	×						
Drug recycling^d^	×	×	×	×	×		

*ADL-BI* activities of daily life on the Barthel Index, *mRS* modified Rankin scale

^a^Accreditation of laboratory examination within 3 days, including head CT, before enrolment

^b^Combined use of drugs before commencing study treatment and continue until the end of the 28-day treatment period

^c^During conservative treatment, if a participant’s neurological function deteriorates associated with an increase in the size of the haematoma and risk of cerebral herniation, they must change over to surgical treatment

^d^Remaining drugs are to be recycled

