## Statistics methods

### Statistical methods for primary and secondary outcomes {20a}

The primary analysis will be performed according to the intention-to-treat (ITT) principle, comprising all randomized participants. A per-protocol analysis will also be undertaken for all participants who have taken at least one dose of the trial medication and complete at least one follow-up assessment. The description of indicators will be by number of cases (and percentages) for categorical variables, and mean (standard deviation) or median (interquartile range) for continuous variables. The chi-square test and logistic regression with adjustment for site, age, sex and baseline haematoma volume will be adopted for the comparison of the primary outcome between the treatment groups. For secondary outcomes, Student’s *t*-test or non-parametric Wilcoxon tests will be performed for continuous outcomes and the chi-square test for dichotomous outcomes. Ordinal logistic regression will be used for the analysis of the shift in the full range of scores on the mRS. All statistical tests are two-sided, with a *p*-value < 0.05 indicating statistical significance. All analysis will be conducted using SAS 9.4 (SAS Institute Inc., USA).

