### SAE reporting and harms {22}

A serious adverse event (SAE) is defined as an event causing or with potential to cause significant harm or requiring medical intervention, whether or not it is considered related to the study treatment. A non-serious adverse event is defined as any undesirable medical experience occurring to a patient, including abnormal laboratory values without clinical consequences.

All SAEs are to be reported within 24 h of the site investigator becoming aware, and a full report is to be filled to the sponsor and the state food and drug administration (SFDA). The ethics committee of pharmaceutical affairs of ONET will conduct an investigation to confirm the causes of an SAE, decide whether the participant can continue with the study medication and deal with the related participants’ complications and adverse events. All patients are to be followed up according to the intention-to-treat principle. The SAE should be documented in the medical records or patient file and signed and dated by the investigator, for audit and monitoring. Safety outcomes are reported to the presiding Ethics Committees in line with their requirements every 6 months, as well as for review by the DMSB at each meeting.

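### Haematoma-volume reduction has no rule for scans after surgery, so evacuation counts as reduction and dilutes a drug effect that works by avoiding surgery

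*Protocol article*

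**What the plan says.** All references are to the protocol article.

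- **Volume outcome.** Outcomes {12} lists "reduction in haematoma volume at 14, 28 and 90 days" among the secondary outcomes, without saying what happens once a patient has been operated on. The primary outcome in the same section does build surgery in: "any reduction in subdural haematoma volume from baseline and free of surgery and death within 28 days of the treatment".
- **Follow-up after surgery.** The section on discontinuing or modifying interventions {11b} says that after an operation "the randomized oral study medication is to be resumed as soon as possible after the operation". The harms section {22} adds: "All patients are to be followed up according to the intention-to-treat principle".
- **Imaging.** Under concomitant care {11d}, "CT scans are performed at end of 2 weeks, 4 weeks and 3 months". Neither that section nor Table 1 exempts operated patients.
- **Routes to surgery.** Table 1 footnote c covers patients who deteriorate with haematoma growth and herniation risk during treatment: "they must change over to surgical treatment". The intervention description {11a}, item iv, allows surgery when the volume has increased at the end of treatment.
- **Analysis.** For secondary outcomes, section {20a} names Student's t-test or says that "non-parametric Wilcoxon tests will be performed for continuous outcomes and the chi-square test for dichotomous outcomes". The missing-data section {20c} carries the last observation forward for missing 4-week data. It does not mention scans that exist but follow an operation.

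**The concern.** A scan after evacuation is not missing, so the stated missing-data rule leaves it in. It shows a small haematoma because the clot was removed, yet it enters the comparison as a reduction. The patients concerned are those whose haematoma grew, that is, the treatment failures. A patient operated on at day 10 is a failure in the primary outcome and may be among the better responders on day-28 volume.

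If dexamethasone works, the control arm has more operations and more of these artificial reductions. The bias therefore runs against the arm that avoids surgery, and it grows with the drug's success in avoiding it. Day 90 is most exposed, because operations decided at the end of treatment fall before that scan. A positive primary result could then sit beside an apparently weak volume result for a reason unrelated to the drug.

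**Working it through.** **The plan's own figure.** The article sizes only the primary outcome: 62.6% v 82.6%, two-sided 5%, 90% power, 5% loss. With mean proportion 0.726:

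n = [1.96·√(2·0.726·0.274) + 1.2816·√(0.626·0.374 + 0.826·0.174)]² / 0.20² = 102.4, so 103 per arm.

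With continuity correction this is 113 per arm. Dividing by 0.95 gives 119 per arm, 238 in total, within 2 of the planned 240. The point below does not alter this. After 5% loss, 120 × 0.95 = 114 per arm remain evaluable.

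**Direction.** Let c and t be the proportions operated on before the scan in control and combination, and d the true medical gain. Let evacuation give k·d more reduction than medical control. Then

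observed difference = d × {1 − [c·k − t·(k − 1)]}.

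For k > 1 the bracket is positive whenever control has at least as much surgery as the combination (and some surgery occurs), so the difference shrinks. The sign changes only if c·k − t·(k − 1) > 1:

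- 10% v 5%: k > 0.95/0.05 = 19.
- 20% v 0%: k > 5.
- Every planned primary failure an operation (37.4% v 17.4%): k > 0.826/0.20 = 4.1.

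**Size, model A (all inputs assumed).** Medical mean reduction 20 mL v 26 mL (d = 6), SD 16. Evacuation gives 30 to 50 mL (k = 1.67 to 5). Surgery is unrelated to the patient's course. Without contamination the standard error is 16·√(2/114) = 2.12, 6/2.12 = 2.83, and power is Φ(2.83 − 1.96), about 81%. With post-operative scans included (difference from the formula, t-test power by simulation):

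| Surgery, control v combination | Difference (mL) | Power |
|---|---|---|
| 5% v 2% | 5.0–5.6 | 60–74% |
| 10% v 5% | 4.2–5.2 | 45–69% |
| 15% v 5% | 2.7–4.7 | 20–63% |
| 20% v 5% | 1.2–4.2 | 8–51% |

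Example, 15% v 5% with k = 5: 6 × {1 − [0.75 − 0.20]} = 2.7 mL.

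**Size, model B (all inputs assumed).** This is closer to the protocol's routes to surgery, because the worst courses are operated on. Baseline 60 mL (SD 25), control mean reduction 20 mL, residual SD 18, 25% of the clot left after surgery. The nominal gain is 8 mL, about 7.0 mL once reduction is capped at baseline volume. Uncontaminated power is 87–88%.

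| Surgery | Estimate (mL) | t-test | Plain Wilcoxon | Surgery ranked worst |
|---|---|---|---|---|
| 5% v 2% | 5.0 | 62% | 66% | 86–91% |
| 12% v 4% | 3.0 | 28% | 35% | 86–91% |
| 15% v 5% | 2.4 | 18% | 25% | 86–91% |
| 20% v 8% | 1.2 | 9% | 13% | 86–91% |

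(The last column gives one range for all four rows.) A milder variant that keeps the full 8 mL gave t-test power of 40%, 29% and 18% for the last three rows. At 3% v 1%, power was about 76–78%.

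**Primary outcome window.** The primary requires patients to be "free of surgery and death within 28 days of the treatment", while Table 1 allows the deciding CT at Day 28 ± 3, that is, up to day 31. Read literally, a patient operated on at days 29–31 before that CT has no surgery within 28 days and a reduced volume, and so scores a good outcome.

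**The case against.** **Nothing in the article says that post-operative scans are included.** This is correct. Inclusion follows from the outcome definition, the retention of operated patients, the CT schedule and the test, taken together. The sentence about all randomized participants concerns the primary analysis, and an analysis plan not shown may set a rule. What remains is that the article fixes outcome, test and missing-data rule, and that these, followed as they stand, keep the scans in.

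**The magnitude is assumed.** This also stands. Eligibility screens out patients thought likely to need surgery, so low rates are plausible, and at 3% v 1% the loss is modest. Exposure should be least at day 14. The direction holds in every case tried.

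**A reader might infer that the bias could reverse the volume result.** The article does not support that. In model A the sign changed only at the extreme, at 25% v 5% and 30% v 8% with evacuation worth 50 mL (−0.3 and −1.1 mL). Model B showed no reversal.

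**A reader might also infer that the primary analysis is compromised.** It is not. Surgery within 28 days is already a failure there. The gap at days 29–31 is small, because the end-of-treatment decision follows a repeat CT and footnote c refers to growth, which implies imaging before most operations.

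**Ranking surgery as worst overlaps with the separate surgery outcome and the primary composite.** This is partly true and is a cost of the remedy. It does not justify crediting evacuation to the drug.

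**Conclusion.** The point holds as a weakness of moderate severity in one secondary outcome. As written, volume reduction mixes the effect of the drugs with the effect of an operation that follows treatment failure, and the observed difference is diluted if the combination prevents surgery.

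Under the assumed inputs, power drops to about 60–75% at surgery 5% v 2%. At 15% v 5% it drops to about 18–30% when surgery falls on the worst courses, or 20–63% when surgery is unrelated to the course. Choosing Wilcoxon over the t-test recovers little. None of these sizes can be derived from the article, and reversal of sign should not be claimed. The sample size stands. The primary outcome needs only a clarifying clause.

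**What to change.** State in the outcome definition, for days 14, 28 and 90 separately, that scans after surgery are not used as drug-related reductions.

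- **Main analysis.** Rank patients with surgery or death before the scan as worst and compare arms with a Wilcoxon test at each time point.
- **Sensitivity analysis.** Set post-operative volumes to missing and use multiple imputation or a mixed model adjusted for baseline volume. Do not apply last observation carried forward here, since it could put an earlier, more favourable volume in place of the failure.
- **Primary outcome.** Define a good outcome as alive and surgery-free through day 28 or the date of the day-28 CT, whichever is later, so that no post-operative CT can qualify and no operation within 28 days is excused. Few patients should be affected.

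The cost is wording only, settled before unblinding. Surgery and haematoma volume are already on the Table 1 schedule. The operation and CT dates must be available for analysis. The price is that the volume result becomes a rank comparison rather than a mean in mL and overlaps in part with the surgery outcome. Mean reductions among patients not operated on can still be shown descriptively.

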### Participant timeline {13}

Baseline demographic and clinical features, including medical history, severity and type of neurological deficit and physical and biochemical results, are collected at the time of enrolment in the study. Treatment should be initiated immediately after randomization (Table 1). All background care should follow standard guideline recommendations for the management of CSDH in China which includes the withholding of anticoagulation and use of antiplatelet agents and prescribing prophylactic antiepileptic drugs and regular use analgesics. Protocol-mandated assessments will be performed according to the schedule (Table 1), and the study flow chart illustrates key steps in the trial (Fig. 1).

**Table 1 Tab1:** Visit and assessment schedule

Items	Screen	Day 1	Day 7 ± 1	Day 14 ± 1	Day 28 ± 3	Day 90 ± 7	Day 180 ± 7
Informed consent	×						
Inclusion/exclusion^a^	×						
Filling general information	×						
Collect medical history	×						
Concomitant medications^b^	×	×	×	×	×		
Physical examination	×						
Surgery		×	×	×	×	×	×
Neurological symptoms^c^	×	×	×	×	×	×	×
Haematoma volume^c^	×			×	×	×	
mRS^c^	×				×	×	×
ADL-BI					×	×	×
Blood routine	×	×		×	×		
Biochemistry	×	×		×	×		
Coagulation	×	×		×	×		
Vital signs^c^	×	×	×	×	×		
Electrocardiography	×			×	×		
Adverse events		×	×	×	×	×	×
Allocate random number	×						
Drug recycling^d^	×	×	×	×	×		

*ADL-BI* activities of daily life on the Barthel Index, *mRS* modified Rankin scale

^a^Accreditation of laboratory examination within 3 days, including head CT, before enrolment

^b^Combined use of drugs before commencing study treatment and continue until the end of the 28-day treatment period

^c^During conservative treatment, if a participant’s neurological function deteriorates associated with an increase in the size of the haematoma and risk of cerebral herniation, they must change over to surgical treatment

^d^Remaining drugs are to be recycled

**Fig. 1 Fig1:**
[figure not shown]
Flow chart to illustrate the design of the trial. ADL-BI, activities of daily life on the Barthel Index; ECG, electrocardiography; IWRS, Interactive Web Response System; mRS, modified Rankin scale

### Sample size {14}

We estimate a sample size of 240 patients will provide 90% power to detect a treatment effect of 20% absolute improvement in the primary composite good outcome, after considering a 5% loss-to-follow-up at 4 weeks, then 240 patients in total with 120 per group is needed to be recruited for this study and good outcome in the single atorvastatin control group of 62.6% being consistent with the single atorvastatin group of the ATOCH trial (48 of 81) [15], a pilot trial showing 20 of 30 patients had a good outcome in a single atorvastatin group [23] and medical record data showing 9 of 12 patients had a good outcome at a single centre in 2017 [17]. The combined drug treatment effect was assumed to be consistent with the percentage of good outcomes found in 29 of 30 patients in a pilot clinical trial [23] and 95 of 108 patients’ medical records from our single centre showing a good outcome.

### Recruitment {15}

All eligible CSDH patients who present to each participating hospital from the start date are prospectively and consecutively enrolled into the study.

## Assignment of intervention: allocation

### Sequence generation {16a}

Eligible patients are centrally randomized in a 1:1 allocation ratio to the intervention (atorvastatin combined with low-dose dexamethasone) and control (atorvastatin combined with matching placebo) groups using a blocked randomization method via a data acquisition system for electronic data capture (DAS for EDC, version 5.0) developed by Stemexcel Technology Co. Ltd., Beijing.

### Concealment mechanism {16b}

DAS for Interactive Web Response System (IWRS) is used to assign the randomization number to the treatment allocation and drug distribution, and each centre will compete to recruit subjects.

### Implementation {16c}

Study medication is provided free of charge to participants: atorvastatin by Pfizer Inc. and dexamethasone by Tianjin Pacific Pharmaceutical Co. Ltd. (Tianjin, China). The placebo dexamethasone, which is composed of dextrin and with the same weight and appearance as dexamethasone, is made by Tianjin Pacific Pharmaceutical Co. Ltd. (Tianjin, China), which has a certification of Good Manufacturing Practice (GMP) for pharmaceutical products issued by the State Food and Drug Administration of China.

Study medication is packed identically and labelled ‘for clinical study use only’ with a packaging number, verification code, dosage, specifications, storage, batch number, duration of usage and manufacturer. A statistician and staff independent of the study research team oversee the packaging of the study medication, with the use of a package number and drug verification code on the tag. Each participant is allocated a unique number to be applied to a drug package number for dispensing and consistency in the database.

